### Student Behavioural Intentions

The survey includes four items assessing behavioural intentions related to consent and bystander intervention. Participants are presented with statements beginning with "I would..." and are asked to rate their responses on a 4-point Likert scale (ranging from 0 to 3), indicating their anticipated frequency of engagement in each behaviour.

### Implementation outcomes

In line with Medical Research Council Guidelines for complex interventions, a comprehensive process evaluation will take place, using mixed methods approaches to examine intervention reach, retention, fidelity, acceptability, and sustainability.

Reach, Retention and Fidelity-facilitators delivering the intervention will record student attendance and other challenges or patterns of implementation using fidelity sheets. These sheets will be completed by facilitators after each student session.

Acceptability and sustainability-assessed via interviews with students, facilitators and other key stakeholders.

## Participant timeline

[figure not shown]

**Figure 2:** Study flow chart

All students will complete a baseline survey before randomisation, immediately-post intervention, and again at 6-month follow-up. A baseline survey will be completed by students before the commencement of the program in schools. An immediate-post survey and later a 6-month follow-up survey will also be administered. Students will complete the surveys in their own time online through REDCap, and each survey will be open for one

week. Students whose parents/caregivers have consented to their participation will be provided with a Participant Information and Consent Form (PICF) beforehand explaining the purpose of the research and its attendant risks and benefits, as well as the secure and confidential handling of their data. Students who consent to participate will receive a baseline survey which will collect data on demographic and potential confounder variables, as well as hypothesised outcome variables. Immediate-post surveys will contain the same hypothesised outcome variables. Six-month follow-up surveys will contain an additional item intended to collect self-reported data on which program sessions the students found most impactful.

## Sample size

A parallel, two-group cluster-randomized design will be used to test whether the Group 1 (Intervention) knowledge average level ( $\mu_1$ ) is greater than the Group 2 (control) average level ( $\mu_2$ ) ( $H_0: \delta \leq 0$  versus  $H_1: \delta > 0$ ,  $\delta = \mu_1 - \mu_2$ ). Based on similar school-based dating violence prevention interventions in the USA (Lee & Wong, 2020), the assumed effect size for the primary outcome (knowledge) is 0.566, corresponding to a standardised mean difference (SMD) of 0.566. To detect this mean difference with 80% power, 6 clusters will be assigned to Group 1 and 6 to Group 2. The required average sample size per cluster is 12 for both groups, yielding a total of 72 subjects per group. Sample size calculations were performed using PASS 2024 (version 24.0.1).

The comparison will be conducted using a one-sided t-test, with degrees of freedom based on the total number of subjects and a Type I error ( $\alpha$ ) of 0.025. Assumptions include a common subject-to-subject standard deviation of 1, an intra-cluster correlation coefficient of 0.026, and a coefficient of variation for cluster sizes of 0.70926. To account for an estimated student dropout rate of approximately 20%, the required average sample size per cluster is increased to 15, resulting in a total of 180 students.

## Recruitment

The secondary schools will be recruited by Laurel House, leveraging their existing networks to directly recruit eligible schools. Many schools have shown interest in offering the program ( $n=12$  with student numbers approx. 900). The research team will gain consent from parents/caregivers prior to their young persons' participation in the trial.

## Assignment of intervention

### Allocation-Sequence generation, concealment mechanism, implementation and blinding

Schools (clusters) will be randomised using a remote system set up by the LTU Statistics Platform. The allocation sequence will be stored on a secure server and concealed from all personnel involved in the trial. It will be created, using computer-generated random numbers, by a statistician with no link to, or contact with, any of the participating schools.

Randomisation will be stratified by the following five variables:

1. Year 9 student population (size)
2. Region of Tasmania
3. Index of Relative Socio-Economic Disadvantage, by suburb and locality (IRSD)
4. Indigenous enrolment, percentage
5. Index of Community, Socio-Educational Advantage (ICSEA)

Once all schools have been confirmed and baseline forms completed, LH will contact the Statistics Platform requesting the randomised assignment of all schools. These assignments will then be communicated to the schools by FH. Prior to baseline form completion all trial team members, schools, and students will be blinded; after this point, all will be unblinded.

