### **Choice of comparators**

To better understand the role of consent and healthy relationships education in the prevention of sexual violence, we will measure outcomes across 12 schools in Tasmania, Australia. Of the 12 schools, six schools will be randomly assigned to the intervention group and six schools to the waitlist control group. The control group will not receive the prevention program during the trial, but for ethical reasons will receive the intervention in 2026 after the study has concluded.

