## Trial design

A parallel two-arm cluster RCT will be conducted among Year 9 students aged 13-15 years old in 12 secondary schools across Tasmania, Australia from 2025 to 2026. With assistance from a statistician, and using minimisation and stratified randomisation techniques, schools will be 1:1 allocated to either a sexual violence primary prevention intervention (SEP), or to a waitlist control group. The level of randomisation will occur at the school level (cluster), rather than the individual level, because of the high risk of contamination in schools where students are routinely interacting. A comprehensive process evaluation and realist evaluation will be conducted alongside the cluster RCT.

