#### Eligibility criteria

The inclusion criteria are:

- 1) students attending public secondary schools in Northern Tasmania, Australia
- 2) students in Year 9-aged 13-15 in these schools, unless their parent/caregiver opt-out of their participation in the trial.

The exclusion criteria are:

- 1) students attending private schools,
- 3) students whose parents opt-out of their participation in the trial.
- 4) students outside Year 9

SEP will be delivered in schools that are both socio-economically and socio-educationally disadvantaged, and are in regional, rural and remote areas of northern Tasmania.

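### Stratifying 12 schools on five variables gives at least 32 strata, does not secure six schools per arm, and does not match the minimisation named under Trial design

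*Protocol*

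**What the plan says.** The method of allocation is described in two places in the protocol.

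- **Trial design:** a statistician assists and, "using minimisation and stratified randomisation techniques, schools will be 1:1 allocated".
- **Allocation-Sequence generation, concealment mechanism, implementation and blinding:** "Randomisation will be stratified by the following five variables". The list is Year 9 size, region, IRSD, share of Indigenous enrolment and ICSEA. Of the sequence it says: "It will be created, using computer-generated random numbers, by a statistician with no link to, or contact with, any of the participating schools". Minimisation is not mentioned here. No categories, block structure or constraint on the totals are given. Assignment of all schools is requested in one step, once every school is confirmed and baseline forms are complete.

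The numbers per arm are fixed elsewhere. Under Choice of comparators, "six schools will be randomly assigned to the intervention group and six schools to the waitlist control group". Under Sample size, "To detect this mean difference with 80% power, 6 clusters will be assigned to Group 1 and 6 to Group 2".

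**The concern.** Stratified randomisation balances arms only within strata that hold at least two units. With more strata than schools, most occupied strata hold one school, and that school's arm is in effect a coin toss. The stratification then does little, and nothing in the stated rule holds the total at six per arm.

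The two sections also do not describe one procedure. Minimisation chooses each assignment from the characteristics of the units already assigned. A stored sequence of random numbers within strata does not. Neither section says which of the five variables are strata and which, if any, are minimisation factors.

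With six schools per arm, balance secured at allocation is the main protection against chance differences between schools. The Sample size section assumes a coefficient of variation of 0.70926 for cluster size, so it expects schools to contribute very unequal numbers. The Statistical methods section adjusts estimates for clustering and names no school-level covariate, so it states no later correction for imbalance. An allocation cannot be redone once schools have been told.

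**Working it through.** **1. The plan's own sample size.** Inputs from the Sample size section: SMD 0.566, SD 1, ICC 0.026, CV of cluster size 0.70926, mean of 12 students per school, 6 schools per arm, one-sided alpha 0.025, degrees of freedom from subjects (144 − 2 = 142).

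- Design effect = 1 + ((1 + CV²)m − 1) × ICC = 1 + (1.503 × 12 − 1) × 0.026 = 1.443.
- SE = √[(1.443/12) × (1/6 + 1/6)] = 0.200, so the non-centrality is 0.566/0.200 = 2.83.
- Power from the non-central t is 80.2%. With 11 students per school it is 77.7%. The stated 12 per school and 80% power are reproduced, and they rest on the 6:6 split.

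**2. Number of strata.** Levels are not stated. Two per variable is the fewest possible: 2⁵ = 32. One variable at three levels gives 48, and all five at three levels give 3⁵ = 243. If region had only one level, 2⁴ = 16 would remain, still more than 12.

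**3. How full the strata are.** With 32 equally likely strata, the expected number of schools alone is 12 × (31/32)¹¹ = 8.5. The expected number of occupied strata is 32 × [1 − (31/32)¹²] = 10.1.

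**4. Resulting split.** Simulated with blocks of two within strata (assumed). Simple randomisation is exact: P(6:6) = 924/4096 = 22.6%, and P(8:4 or worse) = 1 − (924 + 2 × 792)/4096 = 38.8%.

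| Method | P(6:6) | P(8:4 or worse) |
|---|---|---|
| Simple randomisation | 23% | 39% |
| 32 strata, independent factors | 27% | 30% |
| 32 strata, factors correlated 0.5 | 30% | 26% |
| 32 strata, factors correlated 0.7 | 32% | 21% |
| 16 strata | 31% | 23% |
| 243 strata | 23% | 38% |
| Minimisation, five factors, deterministic | 88–95% | none seen |
| Minimisation, five factors, 0.8 biased coin | 61–69% | 2–3% |

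In each minimisation row, the lower P(6:6) omits the overall arm totals from the imbalance score and the higher one includes them. Neither makes 6:6 certain.

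**5. Balance on the variables.** The measure is the mean absolute difference between arms in the number of schools at a given level, per two-level factor, with independent factors.

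- One coin toss per school: 12 × C(24,12)/2²⁴ = 12 × 0.1612 = 1.93.
- Stratification on 32 cells: 1.61.
- Deterministic minimisation: 0.76 to 0.82.
- Minimisation with the biased coin: 1.09 to 1.14.

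**6. Power at unequal splits.** Same formula as step 1, with 1/a + 1/b in place of 1/6 + 1/6.

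| Split | 1/a + 1/b | Power |
|---|---|---|
| 6:6 | 0.333 | 80.2% |
| 5:7 | 0.343 | 79.1% |
| 4:8 | 0.375 | 75.4% |
| 3:9 | 0.444 | 68.1% |

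Under 32 independent strata, 9:3 or worse occurs in about 9% of allocations.

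**The case against.** The strongest reply is that the Trial design section names minimisation and a 1:1 ratio, and that minimisation is made for several factors and few units. This stands in part. A reader might infer from the strata count that the trial cannot balance its arms or that the 6:6 split is lost. The protocol as a whole does not support that: if minimisation were used, balance would be much better than under stratification. Its 6:6 would be likely but not assured, and the section that governs allocation does not mention it.

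A second reply is that the 27% and 30% depend on blocks of two and two-level factors, neither of which is stated. That is correct. However, the ranges above show little change over plausible choices, and more levels make matters worse. Six per arm is stated as an intention, and a single request for all schools would make it easy to impose. What is absent is any rule that does so.

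A third reply is that cut-points and the algorithm may sit in a randomisation document or an SAP. They may. That does not resolve a disagreement over the type of method within the protocol.

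Three further inferences are tempting but not shown:

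- **Region.** Listing it need not conflict with eligibility limited to "students attending public secondary schools in Northern Tasmania, Australia", because areas within the north may be meant.
- **IRSD and ICSEA.** Listing both is not shown to be redundant. The protocol gives no correlation and describes the schools as disadvantaged in both the economic and the educational sense.
- **Adjustment.** Too few degrees of freedom for five school-level covariates would be a criticism of an analysis that the protocol does not propose.

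**Conclusion.** The point holds in this form. The stated rule, taken literally, creates at least 32 strata for 12 schools and behaves almost like simple randomisation: 6:6 in about 27% of allocations, and 8:4 or worse in about 30%. It does not secure the six schools per arm on which the sample size rests. The Trial design section describes a different procedure, better suited to the problem, which also leaves 6:6 unguaranteed without a total constraint.

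The percentages assume two levels per variable, equally likely independent cells and blocks of two. Correlation up to 0.7 raises P(6:6) only to 32%. The power cost is modest on the protocol's own degrees of freedom: about 1 point at 5:7, 5 points at 4:8 and 12 points at 3:9. The more serious consequence is arms that differ in school size and disadvantage, with no stated adjustment. This is more than missing detail, and it has to be settled before allocation.

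**What to change.** Before allocation, rewrite the Trial design and allocation sections so that both name one feasible method with 6:6 imposed.

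Covariate-constrained randomisation suits this trial best, because all schools are assigned on one request:

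1. After all 12 schools are confirmed and baseline is complete, the independent statistician lists the C(12,6) = 924 possible 6:6 allocations.
2. Each is scored for balance on the same five variables.
3. A well-balanced subset, of a size set in advance, is kept and checked so that no two schools are always together or always apart.
4. One allocation is drawn at random from that subset.

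Minimisation with a random element and a 6:6 constraint is an acceptable alternative. Categories and the scoring rule can sit in a separate randomisation document.

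The cost is a few hours of statistician time, the rewording of two sections, and a check that the constrained set keeps inference valid. No new data are needed, since the protocol already calls for all five variables.

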## Outcome measures

### Student Knowledge

The survey instrument comprises six items assessing participants' knowledge related to relationships and empathy. Respondents indicate their level of agreement with statements such as "I know what a healthy relationship looks like" using a 5-point Likert scale (1 = Strongly disagree to 5 = Strongly agree).

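### Allocation waits for the baseline surveys but balances on neither baseline knowledge nor the number enrolled: a cheap improvement in precision and credibility is left unused

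*Protocol*

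**What the plan says.** The Participant timeline section fixes the order: "All students will complete a baseline survey before randomisation". That survey carries the outcome variables as well as demographics. The allocation section has the assignment of all schools requested in one step: "Once all schools have been confirmed and baseline forms completed". So each school's baseline knowledge and its count of responding students exist at the moment of allocation.

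The same section then states: "Randomisation will be stratified by the following five variables". The five are Year 9 student population, region of Tasmania, IRSD, Indigenous enrolment percentage and ICSEA. The Trial design section describes the method as "using minimisation and stratified randomisation techniques" and adds no further variable.

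On the outcome, the Student Knowledge section says: "The survey instrument comprises six items assessing participants' knowledge related to relationships and empathy". The Statistical methods section compares means across arms and between time points with a one-sided t-test, and adjusts the estimates for clustering. It names no baseline-knowledge covariate.

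**The concern.** A baseline measure of the outcome in the same students is usually among the better predictors of their later score. Here it is in hand before any school is allocated, and the plan does not use it. The plan balances on school-level background variables whose relation to knowledge is not stated. The Year 9 roll stands in for cluster size, although only about 180 of roughly 900 students (20%) are to be enrolled and the assumed variation in cluster size is large.

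If the two sets of six schools start apart on knowledge, the gap passes into the estimate. It enters a post-only comparison in proportion to the baseline-post correlation, and a change-score comparison in the opposite direction through regression to the mean. A visible gap on the primary outcome in the baseline table also weakens the result in readers' eyes. An analysis plan can adjust for the gap later, but it cannot undo the allocation.

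**Working it through.** **Inputs (Sample size section).** Six schools per arm; mean 12 students per school analysed and 15 enrolled; ICC 0.026; CV of cluster size 0.70926; one-sided alpha 0.025; degrees of freedom from subjects; "a common subject-to-subject standard deviation of 1"; target effect "corresponding to a standardised mean difference (SMD) of 0.566".

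**1. The plan's own figure.** Design effect DE = 1 + ((CV² + 1)m − 1) × ICC.
- At m = 12: 1 + (1.503 × 12 − 1) × 0.026 = 1.443.
- SE = sqrt(2 × 1.443 / 72) = 0.200. With 142 degrees of freedom, power is 80.2%.
- 12 / (1 − 0.2) = 15 per school, or 180 students. The stated sample size reproduces.

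**2. Chance baseline difference in the enrolled cohort, no balancing on knowledge.**
- At m = 15: DE = 1 + (1.503 × 15 − 1) × 0.026 = 1.560.
- SE = sqrt(2 × 1.560 / 90) = 0.186. The 95% range is ±0.365 SD, and 0.365 / 0.566 = 64% of the target effect.
- P(|difference| > 0.2) = 28%; P(> 0.25) = 18%.
- Simulation with gamma-distributed cluster sizes gives SD 0.191 and a 95th percentile of 0.376. Rounded: SD about 0.19, range about ±0.37.

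The baseline ICC is not stated, so a range is shown at m = 15:

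| Assumed ICC | SE | 95% range | P(> 0.2) |
|---|---|---|---|
| 0 | 0.149 | ±0.29 | 18% |
| 0.026 | 0.186 | ±0.37 | 28% |
| 0.05 | 0.215 | ±0.42 | 35% |
| 0.10 | 0.265 | ±0.52 | 45% |

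The ICC 0 row also approximates the case where the five listed variables remove all variation between schools. About ±0.29 SD would remain, because most of the gap is between students.

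**3. What balancing would achieve.** There are C(12,6) = 924 possible 6:6 splits. Allocation is drawn at random from the best-balanced 10%.
- Criteria of baseline knowledge and enrolled number only: SD about 0.05, under 1% beyond 0.2 SD.
- Five criteria, knowledge entering as the student-weighted arm difference, the other three simulated as independent: SD about 0.10, about 5% beyond 0.2 SD.
- Five criteria, knowledge entering as unweighted school means: SD about 0.135, about 14% beyond 0.2 SD.

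**4. Effect on the estimate.** At an assumed baseline-post correlation of 0.5, a gap of 0.365 SD moves a post-only comparison by 0.5 × 0.365 = 0.18 SD, and a change-score comparison by the same amount the other way. That is 0.18 / 0.566 = 32% of the target effect. The SD of the estimated post difference by simulation, where *balanced* means five criteria with student weighting and *adjusted* means regression on baseline knowledge:

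| Assumed correlation | Random, unadjusted | Balanced, unadjusted | Random, adjusted | Balanced, adjusted |
|---|---|---|---|---|
| 0.4 | 0.19 | 0.175 | 0.176 | 0.171 |
| 0.5 | 0.19 | 0.172 | 0.167 | 0.163 |
| 0.7 | 0.19 | 0.154 | 0.134 | 0.137 |

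Simulation error is about 0.005. With unweighted school means the unadjusted SD falls only to 0.185 (correlation 0.4) or 0.165 (correlation 0.7). Once the model adjusts for baseline knowledge, balancing adds almost nothing to precision.

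**The case against.** Balancing on school-level background variables is a legitimate choice and nothing here is contradictory. Chance imbalance is ordinary sampling variation: the stated 80% power already allows for it and does not rely on balance in knowledge. Baseline adjustment is the usual remedy and is often left to an analysis plan, which may exist. All of this stands, and it limits the point to an improvement.

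Four stronger readings are tempting and are not supported.
- A reader might infer that the allocation biases the result or inflates the type I error. It does not: the imbalance is random and averages to zero over allocations.
- A reader might infer that the protocol rules out baseline adjustment. It names adjustment for clustering and no baseline-knowledge covariate, but it excludes none.
- A reader might expect balancing to all but remove the gap (SD 0.05). That figure holds for two criteria, not for five.
- A reader might infer that one disadvantage index is redundant because "SEP will be delivered in schools that are both socio-economically and socio-educationally disadvantaged". That says the schools are disadvantaged, not equally so. IRSD is defined by suburb and locality, ICSEA is a separate index, and no correlation between them is given.

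What remains is that the information is available at allocation, costs almost nothing to use, and cannot be used for allocation afterwards.

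**Conclusion.** The point holds as a cheap improvement, not as an error. Under the protocol's inputs the arms have about a 28% chance of starting more than 0.2 SD apart on the primary outcome, and the analysis as written does not say it would correct for this. The cost is in precision and credibility.

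Joint balancing on five variables would lower that chance to about 5% to 14%. The precision gain over an unadjusted analysis is modest, and most of it can be had from baseline adjustment alone. What balancing adds beyond adjustment is mainly a more convincing baseline table.

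The figures assume that the outcome ICC applies at baseline, that cluster sizes follow a gamma distribution with the stated CV, that the other balancing variables are independent of knowledge, and that the baseline-post correlation lies between 0.4 and 0.7. The documents do not give that correlation.

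**What to change.** In the allocation section:
- State the mechanism: minimisation, or constrained randomisation over the 924 possible 6:6 splits with a random draw from an acceptable set. Stratification alone cannot work, since five two-level factors already give 2⁵ = 32 cells for 12 schools.
- Include the student-weighted between-arm difference in baseline knowledge among the criteria.
- Replace the Year 9 roll with the number of students who completed baseline.
- Have one row per school sent to the Statistics Platform with the allocation request.

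In the Statistical methods section, adjust the primary comparison for baseline knowledge. Student-level adjustment needs each student's surveys joined by a study code. The Data management section says REDCap does not link email addresses to responses, so confirm that such a code exists.

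The cost is protocol wording and a 12-row summary after the baseline survey closes. Balance on the remaining school-level variables becomes slightly looser. If IRSD is dropped to keep the count at five, it is no longer balanced directly, so check its overlap with ICSEA across the 12 schools first.
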